## Abstract

**Graphical abstract:**

[figure not shown]

*AF* atrial fibrillation, *OSA* obstructive sleep apnoea, *PFA* pulsed field ablation, *PVI* pulmonary vein isolation.

## Background and rationale

The management of atrial fibrillation (AF) is complex and many patients experience recurrence of symptoms after an invasive treatment with catheter ablation [1]. Although general outcomes of AF ablation have improved over the years, due to innovations of ablation techniques, recurrence of arrhythmias is still experienced by at least one in five patients [2, 3]. The prevalence of AF in Europe is currently estimated at 8 million and is expected to rise to 10 million in a decade [4]. Therefore, more effective therapeutic strategies are required.

Several lifestyle risk factors have previously been identified as promoters of AF. These risk factors include obesity, physical inactivity, sleep apnoea, hypertension, smoking, alcohol use and diabetes mellitus [5–9]. In patients with body mass index (BMI) above 27 kg/m^2^, weight loss and general lifestyle advice leads to cardiac reverse remodelling and a reduction in AF symptom burden [10]. Furthermore, sustained weight loss reverses the natural progression of AF and improves arrhythmia-free survival [11, 12]. Likewise, physical inactivity independently increases the risk of AF [13]. Individuals with better cardiorespiratory fitness have a decreased risk of AF recurrence and experience less severe symptoms [14, 15]. In addition, obstructive sleep apnoea (OSA) has a severe, negative impact on AF treatment. Patients receiving OSA treatment are less likely to progress to more permanent forms of AF [16]. OSA treatment with continuous positive airway pressure (CPAP) significantly decreases AF recurrence rates after pulmonary vein isolation (PVI) [17, 18]. Comparably, beneficial AF outcomes are observed if hypertension is strictly managed, if tobacco use is quitted or if alcohol consumption is decreased [19–21].

The observational ARREST-AF and LEGACY trials clearly demonstrate beneficial effects on ablation outcomes when the management of different risk factors is combined [11, 22]. However, these trials are limited, as they only included patients with BMI above 27 kg/m^2^ and the main focus of intervention was losing weight. Besides, more than half of the included patients had sleep indices matching severe OSA. This OSA rate is higher than in comparable AF cohorts and might explain the beneficial effects of losing weight. Furthermore, participants chose their own treatment allocation, possibly leading to bias to a more motivated and healthy intervention group. It is unclear whether outcomes are generalizable to all patients with lifestyle risk factors referred for AF ablation.

The AHA 2020 scientific statement and ESC/EHRA 2020 guidelines for atrial fibrillation include recommendations on lifestyle focussed treatment as part of the management of AF [4, 23]. However, all the evidence stems from studies treating a single risk factor or from observational studies. In patients referred for AF ablation, the uncertainty in OSA prevalence has led to restrained recommendations. OSA screening is not part of the standard work-up and may only be considered if the cardiologist has a high suspicion for OSA. Evidence is lacking from randomized controlled trials on the effectiveness of an integrated lifestyle and OSA screening programme prior to ablation.

Integrated care reduces morbidity and mortality of AF patients if care is provided by well-trained nurses, because adherence to guidelines is stricter and patient education is more personalized [24–27]. However, this reduction is not as evident in centres that are less experienced with nurse-led care [28]. Before the start of this study, the POP researchers explored patients’ expectations regarding the outpatient clinic on topics, such as behaviour change and education, which led to the creation of different care programmes for the respective risk factors. Specialized nurses were then trained on how to provide direct counselling for AF patients and on how to use the different care programmes.

The goal of the POP trial is to ascertain whether in subjects with a high burden of AF and at least one treatable lifestyle risk factor, implementation of an integral AF clinic, focusing on lifestyle improvement, OSA screening, and on patient education, is beneficial for ablation outcomes. This trial aims to provide more certainty to the current limited evidence regarding the implementation of personalized integrated treatment in current AF care.

## Methods

### Trial design

The POP study is a prospective, open-label, single centre, investigator-initiated, randomized controlled clinical trial (NCT05148338). Eligible patients referred for catheter ablation by other cardiologists in non-interventional hospitals will be randomly assigned in a 1:1 ratio to usual current temporary care or an elaborate lifestyle intervention. If a patient experiences a major reduction in AF symptoms during the pre-procedural work-up, the cardiologist will counsel the patient whether the ablation should be cancelled. Patients from both study groups will undergo a PVI according to common clinical practise. After the ablation or from the moment of the decision of the cancellation of ablation, patients will be followed for 12 months. Follow-up visits will be performed at 3 and 12 months after ablation and consist of a physical examination next to laboratory tests and quality of life questionnaires. A detailed study flow chart is shown in Fig. 1. The trial is non-blinded, since blinding is not possible, given that the treating physician is involved in the multidisciplinary team.

**Fig. 1 Fig1:**
[figure not shown]
Study flowchart of the POP trial (prevention to improve outcomes after PVI). *AF* atrial fibrillation, *QoL* quality of life, *OSA* obstructive sleep apnoea

### Study population

The study will enrol patients with paroxysmal or persistent AF referred for their first catheter ablation. Detailed inclusion and exclusion criteria are displayed in Table 1.

**Table 1 Tab1:** Inclusion and exclusion criteria

Inclusion criteria	Exclusion criteria
Age: 18–75 years Paroxysmal or persistent (shorter than 1 year) AF Referral for first catheter ablation At least one of the following risk factors: BMI ≥ 27 kg/m^2^ LDL-cholesterol > 2.6 mmol/L or total cholesterol > 5.0 mmol/L Hypertension (blood pressure > 130/90 mmHg) Diabetes mellitus with HbA1c ≥ 53 mmol/mol Active smoking Alcohol use > 14 equivalent units of alcohol/week Informed consent	Long-standing persistent AF (persistent for more than 1 year) Permanent AF Asymptomatic AF Prior catheter ablation Paroxysmal AF consisting of one episode with a reversible cause (e.g., fever, surgery, thyroid crisis, ischemic) Severe valvular heart disease Prior or soon foreseen implantation of cardiac device, such as pacemaker or internal cardioverter defibrillator Acute coronary syndrome < 3 months before inclusion Unstable heart failure NYHA class IV, or heart failure necessitating admission < 3 months before inclusion Cardiac surgery < 3 months before inclusion or planned cardiac surgery Malignancy Life expectancy < 1 year Pregnancy

*AF* atrial fibrillation, *BMI* body mass index, *LDL* low-density lipoprotein, *HbA1c* glycohemoglobin, *NYHA* New York Heart Association

The study will be conducted in accordance with the declaration of Helsinki, the good clinical practice, and the applicable regulatory requirements [29]. The locally appointed medical ethics committee has approved the research protocol. All participants will be informed by the investigator and are required to give their written informed consent prior to enrolment.

### Lifestyle interventions

Patients in the lifestyle intervention group will undergo an elaborate risk factor assessment at the nurse-led outpatient clinic. This assessment involves measuring body weight and length, blood pressure, a blood test for cholesterol and diabetes, and a home sleep apnoea test (HSAT). The HSAT is performed with a WatchPAT™ 300, which has previously been validated in a cohort of AF patients [30]. Furthermore, lifestyle behaviour such as physical inactivity, alcohol consumption and smoking are assessed in a structural interview. The risk factor definitions and treatment targets are presented in Table 2. If there are too many risk factors to be treated in a reasonable way for the patient (e.g., it would take too much time and effort), the physician will decide which risk factors will be treated, together with the patient in a shared-decision making approach. During the lifestyle intervention, patients will have approximately 3–5 physical appointments with the nurse–practitioner as well as a 10-min consultation with the cardiologist. Further additional consultations for risk interventions will take place as described in Table 2. The ablation will be scheduled when treatment targets are reached, or, if targets are not reached, at maximally 6 months after study enrolment.

**Table 2 Tab2:** Risk factor interventions and targets in the lifestyle intervention group

Risk factor definition	Target and intervention
Overweight: BMI ≥ 27 kg/m^2^	10% body weight reduction is targeted. Treatment consists of additional consultations with a dietician and a physical fitness and activity programme
Physical inactivity: less than 3,5 h of merely vigorous physical activity per week and limitations during activity	> 3.5 h of physical activity per week is targeted. This is supported by a physical fitness and activity programme guided by a physiotherapist or sport cardiologist
Excessive alcohol consumption: > 8 units a week for women and > 14 units a week for men	We aim for a reduction to ≤ 8 units a week for women and ≤ 14 units a week for men. This is supported by behaviour counselling
Tobacco consumption	Patients should quit smoking. A smoking cessation programme is conducted over 6 weeks by a certified nurse
Hypertension: > 130/90 mmHg	Target blood pressure is < 130/90 mmHg. The lifestyle interventions above and antihypertensive medication are used
Hypercholesterolemia: LDL-cholesterol > 2.6 mmol/L or total cholesterol > 5.0 mmol/L	Target LDL-cholesterol is ≤ 2.6 mmol/L and total cholesterol ≤ 5.0 mmol/L. Above lifestyle interventions and lipid lowering medication are used
Glycaemic control: DM de novo is suspected in patients with HbA1c > 48 mmol/mol and fasting plasma glucose > 7.0 mmol/L	In known DM target HbA1c was < 53 mmol/mol. If DM de novo is suspected, patients are referred to their general practitioner for further treatment. Above lifestyle changes are used. Management is done by treating physician
OSA screening with home sleep apnoea test (WatchPAT™ 300). OSA was suspected if AHI ≥ 5 per hour	Referral to pulmonologist for further OSA diagnosis and treatment

*AHI* apnoea–hypopnoea index, *BMI* body mass index, *DM* Diabetes mellitus, *LDL* low-density lipoprotein, *HbA1c* glycohemoglobin, *OSA* obstructive sleep apnoea

### Lifestyle counselling and education in the intervention group

The AF nurses will collaborate with multiple specialists, such as the electrophysiologist, the sport cardiologist, the dietician and the general practitioner. To achieve successful behavioural changes, consultations will follow the principles of shared decision-making and measurable targets will be set. Patients’ knowledge levels will be reinforced through in-person educational sessions and additional digital content, disseminated via an e-health platform (Philips Engage), tailored and calibrated for this new outpatient clinic. Through the platform, patients may also report AF symptoms, submit home measurements to hospital staff, and easily communicate with staff.

### Usual care

In the usual care group, patients will visit the cardiologist and receive standard treatment according to current guidelines. The cardiologist verifies the patient’s eligibility for ablation and may start additional interventions, such as hypertension management and refer high-risk patients for OSA diagnosis and treatment.

### Ablation

Patients from both study groups will undergo the same ablation procedure with a PFA (Pulsed Field Ablation) catheter (Farawave, Farapulse Inc.). Prior to ablation, patients will use uninterrupted anticoagulation during 4 weeks and are on nil per os 12 h prior to the procedure. The ablation will be performed under conscious sedation with fentanyl, benzodiazepines and propofol. After acquiring ultrasound-guided access to the right femoral vein, the operator will perform a transseptal puncture with a steerable sheath. Patients will be heparinized with an activated clotting time target above 300 s. Fluoroscopy will be used to optimize the PFA catheter position in the pulmonary veins. After the electroporation application, entrance block will be confirmed using the Farawave catheter. In patients with recurrent typical atrial flutter besides AF, an additional cavotricuspid isthmus ablation is performed with a radiofrequency catheter.

### Post-ablation care

Patients of either treatment group will visit the outpatient clinic at 3 months after ablation. At this point, the treating physician will stop any current antiarrhythmic medication. If the patient does not experience any symptoms after ablation, no additional rhythm assessment will be performed, since this will not have therapeutical consequences. In symptomatic patients, arrhythmias will be objectivated with electrocardiogram or multiple holter assessments. If an arrhythmia is confirmed on electrocardiogram or holter after 3 months after the index ablation, patients are offered to recontinue antiarrhythmic medication and to undergo a repeat ablation. Furthermore, patients suffering from persistent AF will undergo cardioversion.

### Endpoints

The primary composite endpoint of the study is the number of hospitalizations for re-ablation and cardioversion from baseline to 12 months after ablation. The conditions for performing a re-ablation and cardioversion are explained above.

Secondary endpoints are the number of hospitalizations for re-ablation, the number of cardioversions, the number of cancelled ablations because of overall symptom reduction, mortality, number of strokes, acute ischemic events, or hospitalizations for heart failure at 12 months after ablation.

Further secondary endpoints include change in weight, blood pressure and laboratory tests at baseline, after the lifestyle intervention (for the intervention group) and at 1 year after ablation. Furthermore, ablation success is determined at 12 months after ablation. The ablation is considered to be successful when patients can stop their antiarrhythmic drugs after 3 months, without having recurrence of symptomatic arrhythmias urging for re-ablation. The elaborate lifestyle changes might negatively affect treatment burden. Treatment burden is the perception of cumulative work a patient has to perform to manage their health, and should, therefore, be limited. Therefore, further secondary endpoints include the change in quality of life and treatment burden from baseline to before ablation, at 3 months, and 12 months after ablation. The patient’s general quality of life will be assessed with the Dutch version of the EuroQol-5D questionnaire. This questionnaire includes 5 health-state measures and is suitable to determine quality-adjusted life-years for a cost–utility analysis [31]. AF-specific quality of life is assessed with the Dutch version of the AF effect on Quality of Life Survey (AFEQT). This questionnaire is suitable for describing AF-related symptoms [32]. Treatment burden will be evaluated with a Dutch translation of the Treatment Burden Questionnaire.

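### The ablation-success rule ties failure to recurrence that calls for re-ablation, and leaves cardioversion and drug restart after month 3 unclassified

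*Protocol article*

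**What the plan says.** The Endpoints section of the protocol article lists ablation success, determined 12 months after ablation, among the secondary endpoints. The ablation is "successful when patients can stop their antiarrhythmic drugs after 3 months, without having recurrence of symptomatic arrhythmias urging for re-ablation".

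Post-ablation care describes what happens around and after the 3-month visit:

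- Drugs are stopped for everyone: "At this point, the treating physician will stop any current antiarrhythmic medication".
- If an arrhythmia is confirmed on ECG or Holter after month 3, "patients are offered to recontinue antiarrhythmic medication and to undergo a repeat ablation".
- In addition, "patients suffering from persistent AF will undergo cardioversion".
- In patients without symptoms, "no additional rhythm assessment will be performed, since this will not have therapeutical consequences".

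Cardioversion is also part of the main outcome: "The primary composite endpoint of the study is the number of hospitalizations for re-ablation and cardioversion from baseline to 12 months after ablation". On blinding, the Trial design section states: "The trial is non-blinded, since blinding is not possible, given that the treating physician is involved in the multidisciplinary team".

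**The concern.** The care pathway names three responses to a confirmed recurrence: drug restart, repeat ablation and cardioversion. The success rule ties failure to only one of them and does not say how the other two are classified.

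Two terms are open. The first is the re-ablation qualifier, which could mean that re-ablation was performed, wanted, offered or clinically indicated. The second is being able to stop drugs, which could refer to the 3-month visit alone or to staying off drugs until month 12. On the first of these, the drug condition separates hardly any patients, because the physician stops the drugs in everyone at that visit.

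Whether a recurrence calls for re-ablation is settled between a physician and a patient who both know the allocation. If willingness to re-ablate differs between the arms, success rates could differ with identical recurrence. The Statistical analyses section compares secondary endpoints by chi-squared or Fisher's exact test, and such a test cannot tell a classification difference from a treatment effect.

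**Working it through.** **No figure to reproduce.** The article gives no expected success rate and no power for this endpoint. The check has two parts: how the wording classifies patients, and how large the effect could be.

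**Step 1: classification.** Take patients with a symptomatic arrhythmia confirmed after month 3. Reading A takes the qualifier to mean that re-ablation was performed. Reading B takes it to cover every confirmed recurrence, because repeat ablation is offered to all of them.

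| Management after month 3 | Primary-endpoint event | Success, reading A | Success, reading B |
|---|---|---|---|
| Re-ablation | yes | no | no |
| Cardioversion alone | yes | yes | no |
| Drug restart alone, re-ablation declined | no | yes if drugs are judged at the 3-month visit only; no if the patient must stay off them | no |

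The second and third rows change with the reading, and the article does not choose between the readings.

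**Step 2: size in one arm.** Inputs:

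- R, the recurrence rate. The only related figure in the article is in Background and rationale: "recurrence of arrhythmias is still experienced by at least one in five patients". I use R = 20% as that lower bound and R = 30% as an assumption. Applying the background figure to confirmed symptomatic recurrence after month 3 is itself an assumption.
- q, the share of these recurrences managed without re-ablation. The article does not give it. Assumed range: 0 to 0.5.

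Formulas:

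- Success if any confirmed recurrence is a failure: 1 − R
- Success under reading A: 1 − R(1 − q)
- Difference: R × q

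| R | q | 1 − R | 1 − R(1 − q) | R × q |
|---|---|---|---|---|
| 20% | 0 | 80% | 80% | 0 points |
| 20% | 0.25 | 80% | 85% | 5 points |
| 20% | 0.50 | 80% | 90% | 10 points |
| 30% | 0 | 70% | 70% | 0 points |
| 30% | 0.25 | 70% | 77.5% | 7.5 points |
| 30% | 0.50 | 70% | 85% | 15 points |

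These are upper figures for each q. If a drug restart counts as failure, only patients who had neither re-ablation nor a restart contribute to the excess. Under reading B the difference is zero throughout.

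**Step 3: difference between arms with equal recurrence.** Under reading A, success in the intervention arm minus success in the control arm is R × (q in intervention − q in control). With q = 0.50 in the intervention arm and 0.25 in the control arm:

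- R = 20%: 90% − 85% = 5 points
- R = 30%: 85% − 77.5% = 7.5 points

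Reversing the two shares gives −5 and −7.5 points. The direction is therefore as much an assumption as the size.

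**The case against.** A reader might infer that the success rate is inflated and that patients who restart drugs are counted as successes. The article does not support either as a flat statement.

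- **Drug restart.** Success is determined at 12 months, so being able to stop can naturally be read as coming off drugs and staying off. A patient who restarts would then be a failure. This stands: the text is ambiguous on restart and does not clearly count it as success.
- **The qualifier.** Repeat ablation is offered for any arrhythmia confirmed after 3 months, and the Endpoints section refers back to those conditions. Every confirmed recurrence might then qualify, with no inflation. This reading is possible, but it makes the qualifier redundant, and calling for re-ablation is not the same as being offered it.
- **Disagreement with the primary endpoint.** The primary endpoint counts from baseline, so a patient cardioverted before ablation or in the first 3 months can properly have a primary event and still be a success. This stands. Only cardioversion after month 3 is in question.
- **Size.** The shares managed without re-ablation, and any split between arms, are assumed. This stands.
- **Visibility.** Re-ablations and cardioversions are also separate secondary endpoints, so a shift from one to the other would show there. That helps interpretation but does not settle who is a success.

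Leaving detail to a fuller document is not an answer here, because the article states the success rule itself and the difficulty lies in its wording.

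**Conclusion.** The success rule is poorly fixed. Read literally, it lets a confirmed recurrence after month 3 that is managed by cardioversion alone pass as a success, and it does not settle the status of a drug restart. Because the qualifier rests on unblinded judgement, classification could differ between arms with equal recurrence.

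The bias is possible, not shown. At R = 20% and q from 0 to 0.5, success would be overstated by 0 to 10 points relative to a rule that fails any confirmed recurrence. This rests on an assumed q and on reading the qualifier as re-ablation performed. The article fixes neither.

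The point concerns one secondary endpoint and leaves the primary analysis untouched. It is still worth correcting before the data are seen, because the trial's stated goal is ablation outcomes.

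**What to change.** Drop the re-ablation qualifier. Define failure as any of the following between month 3 and month 12 after ablation:

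- symptomatic atrial arrhythmia confirmed on ECG or Holter;
- cardioversion;
- re-ablation;
- restart of antiarrhythmic drugs.

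Success is the absence of all four. This changes how patients are classified for analysis, not how they are treated.

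**Cost.** One secondary endpoint is reworded, and the reported success rate may be lower. No new visits are needed. Re-ablation and cardioversion are already endpoints, and the pathway already calls for ECG or Holter in symptomatic patients. Drug restart is not named in Table 3, so it must be taken from the clinical-history assessment at 12 months.

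**What remains.** Cardioversion, re-ablation and drug restart are still open-label decisions. After month 3 rhythm is checked only when there are symptoms, and Table 3 lists no 12-month ECG. The change removes one subjective classification step, so it reduces the dependence on unblinded judgement without removing it.
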